## Abstract

**Background:**

The use of remote consultation modalities has exponentially grown in the past few years, particularly since the onset of the COVID-19 pandemic. Although a huge body of the literature has described the use of phone (tele) and video consultations, very few of the studies correspond to randomized controlled trials, and none of them has assessed the safety of these consultation modalities as the primary objective. The primary objective of this trial was to assess the safety of remote consultations (both video and teleconsultation) in the follow-up of patients in the hospital setting.

**Methods:**

Multicenter, randomized controlled trial being conducted in four centers of an administrative healthcare area in Catalonia (North-East Spain). Participants will be screened from all individuals, irrespective of age and sex, who require follow-up in outpatient consultations of any of the departments involved in the study. Eligibility criteria have been established based on the local guidelines for screening patients for remote consultation. Participants will be randomly allocated into one of the two study arms: conventional face-to-face consultation (control) and remote consultation, either teleconsultation or video consultation (intervention). Routine follow-up visits will be scheduled at a frequency determined by the physician based on the diagnostic and therapy of the baseline disease (the one triggering enrollment). The primary outcome will be the number of adverse reactions and complications related to the baseline disease. Secondary outcomes will include non-scheduled visits and hospitalizations, as well as usability features of remote consultations. All data will either be recorded in an electronic clinical report form or retrieved from local electronic health records. Based on the complications and adverse reaction rates reported in the literature, we established a target sample size of 1068 participants per arm. Recruitment started in May 2022 and is expected to end in May 2024.

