**Primary outcome**			
Rate of complications^b^ of the baseline disease	A secondary disease, an accident, or a negative reaction (including adverse reactions to treatment) occurring during the course of the baseline disease and usually aggravating the illness.	Measure: events, as recorded in the eCRF. Metrics and aggregation: event rate (i.e., proportion of patients experiencing an event within each arm and the follow-up period).	Investigator-reported in the eCRF Local EHR.

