**Secondary outcomes**			
Rate of severe complications of the baseline illness	A complication with significant impact on patient’s life and/or that require intervention by a healthcare professional	Measure: events, as recorded in the eCRF. Metrics and aggregation: event rate (i.e., proportion of patients experiencing an event within each arm and the follow-up period).	Investigator-reported in the eCRF Local EHR.
Rate of severe adverse reactions related to the treatment of the baseline condition	An undesired health event related to a drug administered to treat the baseline health condition	Measure: events, as recorded in the eCRF. Metrics and aggregation: event rate (i.e., proportion of patients experiencing an event within each arm and the follow-up period).	Investigator-reported in the eCRF
Rate of preventable hospitalizations	Hospitalizations due to illnesses secondary to the chronic diseases that can be managed in the outpatient setting^c^	Measure: events, as recorded in the eCRF. Metrics and aggregation: event rate (i.e., proportion of patients experiencing an event within each arm and the follow-up period).	Local EHR
Non-scheduled medical encounters related to poor control of the baseline disease	The following events will be considered: • Non-scheduled appointments (phone, videoconference, or face-to-face). • Visits to primary care services. • Visits to the emergency room. • Hospital admissions.	Measure: events, as recorded in the eCRF. Metrics and aggregation: event rate (i.e., proportion of patients experiencing an event within each arm and the follow-up period).	Investigator-reported in the eCRF Local EHR
Pharmaceutical prescriptions	The number of new prescriptions and renewals will be collected, along with the type of pharmaceutical prescription: long-term, acute process, or pro re nata.	Measure: ATC groups prescribed Metrics and aggregation: difference in number of ATC groups between baseline and last visit; the outcome will be measured as the mean and standard deviation, and median and interquartile range (i.e., 25^th^ and 75^th^ percentiles).	Administrative records.

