### Data management and analysis

All data recorded in the eCRF will be stored in a REDCap platform hosted in a local server. The REDCap data will be transferred to a database, which will also contain the data extracted from the local EHR and the CHSS registries. All registries will be linked through the identification number of the Catalan Health Service.

Data recorded in the eCRF will be monitored for completeness and quality by a professional monitor working at the research office of the Hospital acting as sponsor. We will schedule periodic visits to assess the adherence of investigators to the study protocol and good clinical practices. The clinical monitor will release reports at the end of each visit.

A statistical analysis plan, with detailed analyses for each study outcome, will be performed after the last patient has attended the final visit and before the closure of the database.

The primary objective will be assessed using a non-inferiority analysis of the cumulative incidence of complications of the baseline disease between remote consultation (video and teleconsultation arms) and face-to-face consultation, using a non-inferiority margin of 2%. The analysis will be based on a modified binomial test to assess the non-inferiority of an experimental intervention vs. a control group in a three-arm trial [23]. The primary analysis will be conducted on a per-protocol study sample, which will include all participants who have finished the study and have not been withdrawn because of non-allowed visits using modalities other than scheduled. The intention-to-treat population, used for sensitivity analyses, will consist of all randomized patients completing at least one visit. Since the analysis will be based on an event rate, missing data will not be imputed.

The primary analysis will be replicated with patients stratified according to the following characteristics: hospital department, diagnostic, disease duration (chronic vs. acute or sub-acute), anatomic-therapeutic treatment groups, and GMA health risk group. The clinical and demographic characteristics of study participants will be described and compared between excluded/withdrawn participants.

The statisticians will be blinded for the allocation arm. The type I error will be set at 2.5% for the primary analysis and 5% for the rest of the analyses. All analyses will be conducted using R software (version 4.0 or higher) [24]. Data collected during the ECASeT trial will not be re-used.

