### Sample size considerations

The sample size was estimated based on the primary endpoint of cumulative incidence of complications related to the baseline disease. The sample size analysis was computed with R software [24], following the approach described by Steen A. Julious for non-inferiority trials [25]. Although there is little available information regarding this outcome in the general population of chronic patients, we expect 10% of events in face-to-face consultations [26–28] and 12% in the remote consultation arm (based on routine practice of the research team). Assuming a type-I error of up to 2.5% and a statistical power of 80%, 1068 subjects per arm should be analyzed to reject the non-inferiority hypothesis with a non-inferiority margin of 2% and assuming 10% of participants lost to follow-up.

Altogether, the participating centers schedule 252,000 routine follow-up visits during a period equivalent to the study, corresponding to 121,400 different patients. Therefore, the recruitment of the estimated 2136 patients is considered within the capabilities of the participating centers.

Owing to the scarcity and heterogeneity of available data about the primary endpoint, a blinded interim analysis will be conducted when 50% of the total sample has been recruited to revise the assumptions used to calculate the sample size, as proposed in the E9 Guide of the ICH on Statistical Principles for Clinical Trials [29].

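### Table 1 measures non-scheduled encounters only as any versus none; adding a count per person-time would be a cheap gain

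*Protocol article*

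**What the plan says.** Protocol article, Outcomes and variables, Table 1. Each of the five clinical event outcomes (complications, severe complications, severe adverse reactions, preventable hospitalizations and non-scheduled encounters) has events as its measure and the same metric: "event rate (i.e., proportion of patients experiencing an event within each arm and the follow-up period". The row "Non-scheduled medical encounters related to poor control of the baseline disease" pools unscheduled appointments by any modality, primary care visits, emergency room visits and admissions. No count of clinical events is listed.

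Protocol article, Participant timeline. The final visit is the one nearest to 12 months (plus or minus 2), or earlier on discharge or discontinuation. Patients in the remote arm discontinue if their clinical status comes to need face-to-face care or if they do not follow the remote procedures. Patients in the face-to-face arm discontinue if their health makes travel to the hospital inadvisable.

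On the primary outcome, the Abstract (Methods) states: "The primary outcome will be the number of adverse reactions and complications related to the baseline disease". Data management and analysis plans a "non-inferiority analysis of the cumulative incidence of complications of the baseline disease" with a modified binomial test and a 2% margin. Sample size considerations uses the same quantity: "we expect 10% of events in face-to-face consultations" and "12% in the remote consultation arm".

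**The concern.** A patient with one unscheduled contact and a patient with five count the same under an any/none metric. For non-scheduled encounters this fits poorly. The outcome is meant to show poor control of the baseline disease, and poor control can show as repeated contacts. The metric also takes no account of time at risk, although some patients are observed for much less than 12 months and the reasons for stopping early differ by arm.

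At stake is the sensitivity of a secondary safety outcome. If remote follow-up leads to more contacts per patient, the proportion with any contact may show little of it. Because Table 1 states the metric, this is a choice the article makes and not a detail left open. The analysis plan is due only after the last patient's final visit, so a count first specified there would come after all outcome data are collected.

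Separately, the Abstract's wording leads a reader to expect a count as the primary outcome, which the body of the article does not plan.

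**Working it through.** **Which quantity the trial is sized on.** Inputs from Sample size considerations: 10% and 12%, margin 2%, type I error 2.5% (taken as one-sided), power 80%, 10% loss.

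n = (1.96 + 0.842)² × [0.10×0.90 + 0.12×0.88] / 0.04² = 7.85 × 0.1956 / 0.0016 ≈ 960; 960 / 0.9 ≈ 1067, against 1068 stated.

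The stated figure therefore comes from a formula for two proportions, not for counts. (It is reached only by adding the expected 2-point difference to the margin to give 0.04. That is a separate question, not pursued here.) Table 1, the analysis section and the sample size agree on the proportion, and the Abstract is the outlier.

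**Non-scheduled encounters.** The article gives no encounter rate, dispersion or power for this outcome. Assumptions: negative binomial counts with control mean m and dispersion k; rate ratio 1.2; 961 evaluable per arm (1068 × 0.9); two-sided 5% (the article gives 5% without sidedness).

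- Any/none: P(any) = 1 − (1 + k·m)^(−1/k), or 1 − exp(−m) at k = 0, then a two-proportion test.
- Count: Wald test of the log rate ratio, variance [(1/m₁ + k) + (1/m₂ + k)] / 961.

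At m = 1, k = 1:
- Any/none: 0.500 v 0.545, standard error 0.0228, z ≈ 2.00, power 51%.
- Count: variance (2 + 1.833)/961 = 0.00399, z = 0.1823/0.0632 = 2.89, power 82%.

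At m = 0.3, k = 1:
- Any/none: 0.231 v 0.265, standard error 0.0197, z ≈ 1.72, power 41%.
- Count: variance (4.333 + 3.778)/961 = 0.00844, z = 1.98, power 51%.

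Power, any/none v count, over a wider range:

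| Control mean m | k = 0 | k = 1 | k = 2 |
|---|---|---|---|
| 0.3 | 56% v 63% | 41% v 51% | 32% v 43% |
| 0.5 | 73% v 84% | 48% v 66% | 35% v 53% |
| 1 | 87% v 99% | 51% v 82% | 34% v 65% |
| 2 | 87% v 100% | 46% v 91% | 29% v 72% |
| 3 | 73% v 100% | 39% v 94% | 26% v 75% |

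For k from 0 to 4 the gain at m = 0.3 is 7 to 11 points. With overdispersion (k from 0.5 to 4) and m from 1 to 3, it is about 24 to 55 points.

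**The same check at the primary outcome's level.** With about 0.105 events per patient and the same rate ratio, power is 26.0% v 27.2% at k = 0 and 16.8% v 20.1% at k = 4, a gain of about 1 to 3 points. These are powers to detect a rate ratio of 1.2, not non-inferiority powers.

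If 10% of patients have at least one complication, the share of them with a repeat is 5% at k = 0, 10% at k = 1, 14.5% at k = 2 and 23% at k = 4. Mean events per affected patient are 1.05, 1.11, 1.17 and 1.31.

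**The case against.** The strongest reply has four parts.

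**The proportion with any event is a standard safety metric.** This stands for the primary outcome. A reader might infer that the trial could declare non-inferiority while the remote arm has many more complications in total. Such a case can be constructed, but the article gives no repeat-event frequency, and at 10% affected repeats are few unless dispersion is very high. The result would also need that dispersion in one arm only. An unresolved problem can also register in the severe-complication, hospitalization and encounter outcomes.

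**The encounter gain rests on assumed rates.** This stands too. Encounters count only if related to poor control of the baseline disease, and eligible patients have conditions of moderate complexity that need no physical examination, so the mean may be low. A reader might infer that any/none throws away most of the information on encounters. The documents do not show that.

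**Supportive models belong in the analysis plan, which is not shown.** This stands in part. Their absence from an article is no error, but Table 1 does fix the metric for encounters, so an addition there is a fair suggestion.

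**Counting is harder than it looks.** This stands. Complications are defined broadly without a list, so repeat and continuing events must be told apart. Remote patients who worsen may discontinue, and an offset for follow-up time assumes that stopping is unrelated to outcome.

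On the Abstract, a reader might infer that the primary outcome is undefined. It is not: every operative section uses the proportion.

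**Conclusion.** A cheap improvement, not a flaw in the primary analysis. For non-scheduled encounters, Table 1 names only an any/none proportion although the contacts can recur and follow-up is unequal. A count per person-time would add about 10 power points at a mean of 0.3 encounters per patient and about 31 at a mean of 1, given dispersion 1, a rate ratio of 1.2 and 961 evaluable per arm. All of these except the 961 are assumptions, and the gain is modest if encounters are rare.

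For complications, the proportion with at least one event is sound and fits the 2% margin. A count there is informative support with a negligible power gain. The Abstract's reference to a number is a minor wording inconsistency.

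**What to change.** 1. In Table 1, add the number of non-scheduled encounters per person-time beside the proportion: negative binomial, or Poisson with robust variance, with log follow-up time as offset, reported as a rate ratio.
2. Add a supportive analysis of the number of complications per participant. Keep the proportion with at least one complication as the primary outcome, with its 2% margin and test unchanged.
3. State how a repeat event is told apart from a continuing one, and report follow-up time and reasons for discontinuation by arm beside the rate ratios.
4. Align the Abstract with the proportion used in Table 1, Data management and analysis, and Sample size considerations.

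Cost: a few lines of text and one extra model for each of the two outcomes, with no new data and no change in sample size. Downsides: a dispersion assumption, which robust variance limits; some adjudication of repeat events; and an offset that does not correct for discontinuation related to worsening.

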**Discussion:**

The scarcity of precedents on the assessment of remote consultation modalities using randomized controlled designs challenges making design decisions, including recruitment, selection criteria, and outcome definition, which are discussed in the manuscript.

**Trial registration:**

NCT05094180. The items of the WHO checklist for trial registration are available in Additional file 1. Registered on 24 November 2021.

**Supplementary Information:**

The online version contains supplementary material available at 10.1186/s13063-023-07679-1.

## Introduction

The debut of telemedicine into routine practice stretches back over three decades [1]. However, the use of this modality of care delivery has exponentially grown in the past few years, accompanied by a remarkable body of literature reporting the benefits of different types of telemedicine in the management and follow-up of various chronic and acute conditions [2–6].

The concept of telemedicine encompasses multiple information and communication technologies (ICT) solutions for monitoring patients remotely [7]. Among them, video conferencing and phone calls (commonly regarded as video consultation and teleconsultation, respectively) are candidates to re-shape care pathways in the mid-term, thus mitigating the expected overwhelming of healthcare systems associated with the upcoming demographic shift [8, 9]. In the past 2 years, the public health emergency derived from the COVID-19 pandemic has boosted the implementation of remote consultation systems to avoid crowding of healthcare centers [10–12], thus accelerating the entrance of this modality of care delivery in routine practice.

The rapid implementation of remote consultations in many healthcare systems of high-income countries has not been accompanied by high-quality evidence regarding its effectiveness and safety. Thus, although thousands of studies have described the benefits and usage of various types of remote consultation, very few correspond to randomized-controlled designs, and the assessment of potential harms of remote consultation has been typically listed as secondary—often descriptive—outcomes [13, 14]. We present herein a study protocol of a randomized controlled trial to assess the safety of remote consultations (both video and teleconsultation) in the follow-up of patients in the hospital setting.

## Design

### Study setting and participants

The ECASeT trial (*Ensayo Clínico abierto y Aleatorizado para valorar la Seguridad de la Teleconsulta, frente a la consulta clínica presencial* in Spanish) is aimed at testing safety of remote consultations, based on its non-inferiority compared with face-to-face consultation. The ECASeT trial will be conducted in four centers in the healthcare area of *Alt Penedès-Garraf* in Catalonia (North-East Spain): three secondary hospitals (Hospital Sant Antoni Abat, Hospital Sant Camil, and Hospital Comarcal de l’Alt Penedès) and a rehabilitation center, all part of Healthcare Consortium Alt Penedès Garraf (CSAPG). All study sites belong to the public network of hospitals and primary care centers of the Catalan Health Service and provide universal healthcare to a catchment population of 247,357 inhabitants. Hospital departments from all areas (i.e., locomotive, internal medicine, surgery, gynecology, and pediatrics) are involved in the study.

Participants will be screened from all individuals, irrespective of age and sex, who require follow-up in outpatient consultations of any of the departments involved in the study. Eligibility criteria have been established based on the local guidelines for screening patients for remote consultation [15]. Briefly, to be eligible for remote consultation, patients have to have adequate digital literacy at the physician discretion and technological capacity to use the video conferencing software and undergo a type of follow-up that, due to the moderate complexity of the pathology, does not require physical examinations. Patients followed up in more than three departments, those with visual or hearing impairments that may hamper patient-physician communication, and those enrolled in another clinical trial that requires an experimental intervention during the follow-up will be excluded from the study.

### Interventions

Participants will be randomly allocated into one of the two study arms: control (i.e., face-to-face consultation) and remote consultation (including teleconsultation, and video consultation). All patients, irrespective of the consultation type, will receive short text message reminders a few days before the visit.

Participants allocated into the control arm will be scheduled with face-to-face appointments as usual. All phone calls (except reminders for scheduled visits) performed by the physician during the study will be noted in the electronic case report form (eCRF). Per protocol, participants allocated in the control arm can receive up to 25% of physician-doctor interactions by phone (that is, one phone call allowed for three face-to-face appointments).

Participants allocated in the remote consultation arm will be scheduled remote visits, either phone or video consultation. In case of phone visits, the physician will call the main phone number provided by the patient and, in case of not receiving an answer, other phone numbers listed as contact numbers. In case of video consultation, the participant will receive an additional text message with the visit link. When clicking the link, a website with the video consultation system embedded will open in the default browser of the user. The video consultation platform of the physician pops up a message indicating that the patient is in the virtual waiting room. Patients will remain in the virtual waiting room until the physician starts the visit. A technical assistance is readily available for physicians who experience troubles with the system. In case the patient does not show up to the video consultation after a reasonable time, the physician calls the patient by phone. The date and hour of the phone call and the reason for the inability to connect are recorded in the eCRF.

Participants allocated in the remote consultation arm that require face-to-face visits will be excluded from the per-protocol analysis, and the reason for the face-to-face visit will be recorded in the eCRF. Participants allocated in the remote consultation arm and scheduled with a phone visit cannot be visited by video, whereas those scheduled for a video consultation can undergo up to 25% of phone visits. Phone contacts and their reason in patients in the video consultation arm will be recorded in the eCRF.

Non-scheduled visits will be defined as any contact between the patient and the physician that occurs before the date established in the previous follow-up visit. Non-scheduled visits will be performed according to the study arm and type of remote consultation (i.e., phone or video) in which the patient has been allocated and will be considered for the analysis.

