**Fig. 1 Fig1:**
[figure not shown]
Participant timeline ^a^The frequency of the follow-up visits will be determined by the physician based on the diagnostic and therapy of the baseline disease and will receive a reminder (either SMS or phone call) before each visit. ^b^Either the follow-up visit closest to 12 ± 2 months after enrollment or before in case of discharge or early discontinuation

In addition to voluntary withdrawal, the following situations will lead participants in the remote consultation arms to discontinue the study: a change in their clinical status that requires face-to-face consultation and not following the procedures for remote consultation adequately. Patients allocated in the face-to-face arm will discontinue in case their health status discourages moving to the hospital for follow-up visits. The reasons for ending the study will be recorded in the eCRF.

The study will be temporarily interrupted if the local authorities or healthcare center managers decide to ban or limit face-to-face consultations because of the rapid spread of an infectious agent. This interruption can be partial in case banning face-to-face consultations does not affect all hospital services. The study will resume when face-to-face consultations are restored, and there is enough healthcare activity for adequate recruitment in all study arms. In case of a temporal interruption, the study will be automatically extended for a time that is at least equivalent to the interruption time.

The independent ethics committee can interrupt the study at any time in the advent of risk for participants, and the study sponsor can do it as well because of financial issues.

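### The primary per-protocol set can exclude remote-arm patients because of the outcome itself, under a broader rule than in the control arm, so it can be biased toward non-inferiority

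*Protocol article*

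**What the plan says.** Data management and analysis makes the per-protocol set decisive: "The primary analysis will be conducted on a per-protocol study sample". To belong to it, a participant must have reached the end of the study without being withdrawn over a visit in a modality that the allocation did not permit. The intention-to-treat population (randomised, at least one visit) serves sensitivity analyses only, and missing data are not imputed.

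Two rules remove remote-arm patients on grounds that can be clinical. Interventions: "Participants allocated in the remote consultation arm that require face-to-face visits will be excluded from the per-protocol analysis". Participant timeline, in the text after Fig. 1, lists among the reasons for a remote patient to discontinue: "a change in their clinical status that requires face-to-face consultation and not following the procedures for remote consultation adequately".

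The control arm has different rules. Interventions: "participants allocated in the control arm can receive up to 25% of physician-doctor interactions by phone". Participant timeline adds that a face-to-face patient discontinues when health status makes travel to the hospital inadvisable.

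Table 1 defines the primary outcome as a secondary disease, accident or negative reaction during the baseline disease, typically making it worse. It is summarised as the proportion of patients with an event.

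**The concern.** A complication that worsens the baseline disease is an obvious reason for a doctor to want to examine the patient. In the remote arm that need takes the patient out of the primary analysis. In the control arm the same need is met by the modality already in use, so the patient leaves on health grounds only under the narrower travel rule. Membership of the primary set can therefore depend on the outcome, and more strongly in the remote arm than in control.

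At stake is the error rate of a safety trial. If enough remote patients with complications drop out of the numerator, a remote strategy that sits on or beyond the margin can be declared non-inferior. The Discussion mentions frequent arm switching for care needs, but only as a threat to power, not as a source of bias.

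**Working it through.** **Inputs from the protocol** (Sample size considerations; Data management and analysis): control risk 10%, remote risk 12%, margin 2% (read as absolute), type I error 2.5%, power 80%, 10% loss to follow-up, 1068 per arm. The 2.5% is taken as one-sided, which is an assumption because sidedness is not stated.

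**The plan's own figure.** n = (1.96 + 0.84)² × (0.10×0.90 + 0.12×0.88) / 0.04² ≈ 960. With a pooled rate of 11% it is 961, and 961/0.9 ≈ 1068. The stated number reproduces, but only with a 4-point distance between true difference and margin. That is a separate matter and is not pursued here. The calculations below use 961 per arm.

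**Effect of exclusion.** Let f and g be the shares of patients with and without an event who are excluded from an arm with true risk p.

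- Per-protocol risk = p(1−f) / [p(1−f) + (1−p)(1−g)]
- Patients kept = 961 × [1 − pf − (1−p)g]
- P(declare non-inferiority) = Φ[(0.02 − d)/SE − 1.96], where d is remote minus control per-protocol risk and SE is the unpooled standard error

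The protocol gives no value for f or g, so all values below are assumptions.

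**One case in full** (f = 20%, g = 0, control untouched). Remote risk = 0.096/(0.096 + 0.88) = 9.84%. Patients kept = 961 × 0.976 = 938. d = −0.0016. SE = √(0.0984×0.9016/938 + 0.10×0.90/961) = 0.0137. (0.02 + 0.0016)/0.0137 − 1.96 = −0.38, and Φ(−0.38) = 35%.

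**Range**, true risks 12% and 10%, so the true difference lies on the margin and the nominal error is 2.5%:

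| Remote f | Remote g | Control f | Control g | Remote risk | Control risk | Difference (points) | False non-inferiority |
|---|---|---|---|---|---|---|---|
| 0 | 0 | 0 | 0 | 12.0% | 10.0% | +2.0 | 2.5% |
| 10% | 0 | 0 | 0 | 10.9% | 10.0% | +0.9 | 12% |
| 20% | 0 | 0 | 0 | 9.8% | 10.0% | −0.2 | 35% |
| one third | 0 | 0 | 0 | 8.3% | 10.0% | −1.7 | 79% |
| 20% | 10% | 0 | 0 | 10.8% | 10.0% | +0.8 | 13% |
| 20% | 10% | 10% | 5% | 10.8% | 9.5% | +1.3 | 7% |
| 20% | 5% | 20% | 5% | 10.3% | 8.6% | +1.7 | 4% |
| 20% | 20% | 0 | 0 | 12.0% | 10.0% | +2.0 | 2.5% |
| 10% | 20% | 0 | 0 | 13.3% | 10.0% | +3.3 | 0.3% |

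**How few patients it takes.** With g = 0, the remote per-protocol risk falls to 10% when 0.12(1−f)/(1−0.12f) = 0.10, so f = 0.02/0.108 = 18.5%. That is about 21 of 115 remote event patients, or 2.2% of the arm.

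The inflation comes from exclusion that is both related to the outcome and unequal between arms. Where either feature is absent it largely or wholly disappears.

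**The case against.** Much can be said for the plan. Per-protocol primary with an intention-to-treat check is a familiar non-inferiority design, because intention-to-treat can dilute a real difference. The link from complication to exclusion is also loose. Complications are graded from mild, needing no medical follow-up, and non-scheduled visits take place in the allocated modality and count in the analysis. Nothing says that an emergency or primary-care attendance is an excluding visit. Remote patients are also removed for not following procedures, which need not involve an event, and control patients can be lost on health grounds too. All of this stands, and it is why the effect is stated as possible and its size as a range that includes none. The dilution argument supports looking at both sets. It does not justify removing patients because of the outcome.

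It can also be said that the analysis plan, not shown, may settle whether events before exclusion count. But the exclusion is a rule the protocol states, so that plan would have to override it and not merely fill a gap.

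A reader might infer more than the document supports:

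- That a control patient with the same complication always stays in. The travel rule in Participant timeline says otherwise.
- That the sensitivity analysis is run at a laxer level, from "The type I error will be set at 2.5% for the primary analysis and 5% for the rest of the analyses". Sidedness is not given. One-sided 2.5% and two-sided 5% yield the same bound, and a sensitivity analysis of the primary may fall under the primary level.
- That requiring at least one visit guts the intention-to-treat set. The screening visit counts as the baseline visit, so this may exclude almost nobody.
- That requiring patients to have finished removes deaths. Death is not addressed, the requirement applies to both arms, and the final visit may come early on discharge or discontinuation.

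**Conclusion.** The concern holds in conditional form. The stated rules let exclusion from the primary set depend on the primary outcome, more broadly in the remote arm than in control, and the analysis that would reveal this does not decide the result. No rule says which prevails if the two sets disagree.

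The likely direction is toward non-inferiority, since a remote patient who needs examination leaves while a control patient with the same need usually does not. That direction is not certain: exclusions mainly for technical or adherence reasons would dilute or reverse it. Under the protocol's 12% and 10%, 961 per arm and an assumed one-sided 2.5%, plausible exclusion patterns give a false non-inferiority rate anywhere from below 2.5% to 79%. The document cannot narrow that range. The statement that the plan does delete events and does bias the result goes further than it allows.

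This should be settled before the analysis, because a small number of outcome-related exclusions is enough to remove the whole 2-point difference.

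**What to change.** Change the analysis rules only. The clinical rules for switching modality or discontinuing stay as they are.

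1. In every analysis set, count any complication that preceded or led to a face-to-face visit or discontinuation. Do not remove a patient from the per-protocol set for an off-modality visit triggered by a complication. The reason for each face-to-face visit in the remote arm is already to be recorded in the eCRF.
2. Require the upper confidence bound for remote minus face-to-face to lie below the 2% margin in both the as-allocated intention-to-treat (all-randomised) set and the per-protocol set, each at one-sided 2.5%. For discontinued patients, take events from the local EHR through the planned follow-up period.

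The protocol schedules the statistical analysis plan after the last final visit and before database closure, so the wording can be fixed there and notified as an amendment.

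Costs: non-inferiority becomes harder to claim, and patients who switch count under their allocated arm. Later EHR events must be attributed to the baseline disease. That last item is real work: the Discussion plans EHR screening within the follow-up period, which may end at discontinuation, so capture after that point is not shown to be in hand.
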